### Randomisation and Device Activation

The randomisation and device activation visit will take place between 2 and 4 weeks post-implantation, pending proper wound healing.

Firstly, the following will be performed by blinded study personnel:
Participants will be assessed to determine whether they have experienced any adverse events, and a case report form (CRF) will be completed, as applicable.New x-ray images will be taken to record the lead locations.Participants will be provided with a multi-day diary and instruct to record their VAS pain scores daily for 7 days prior to the 1-month follow-up.The participant’s device and lead will be programmed according to their allocated group; whereas the lead is different, the programming parameters used are identical and can be found in Fig. 2.

At this point, the participant enters the ‘follow-up’ phase of the study, with visits at 1, 3 and 6 months. These visit frequencies mirror our standard of care for routine clinical practice.

During these visits, all participants will be asked to complete the following questionnaires in addition to bringing their multi-day pain diary:
Pain severity on a 0-100 mm (VAS)Pain mapOswestry Disability Index (ODI v2.1a)Patient Health Questionnaire 9 (PHQ-9)Pittsburgh Sleep Quality Index (PSQI)EQ.5D-5 LPain medication usagePatient Global Impression of Change (PGIC)Participant satisfactionSensation map.

Any adverse events are monitored and documented in the CRF. An X-ray may be taken if there are any concerns about lead migration.

To check fidelity of blinding, participants and assessors will be asked to guess their treatment allocation at the end of the study. We will monitor potential outcome assessor blinding by asking them to guess each patient’s allocation at the end of each follow-up assessment. After the trial is completed, we will compare actual and anticipated treatment allocations.

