#### Identification and Description of the Investigational Device

The Senza™ System, a totally implantable SCS system that is intended to aid in the management of chronic intractable pain, received a European Union (EU) CE Mark in May 2010.

The Senza System consists of a rechargeable implantable pulse generator (IPG) with 16 output channels. The IPG is implanted in a subcutaneous pocket and is capable of stimulating the spinal cord nerves when used with one or two 8-contact percutaneous leads. The IPG is controlled by a patient remote and/or a clinician programmer.

Lead(s): The percutaneous lead has eight contacts.

Extension(s): An extension may be used during the permanent implantation procedure, to connect the lead to the IPG.

IPG: The IPG is a rechargeable stimulator with 16 output terminals. Each of the 16 outputs can be programmed as a cathode or an anode. The IPG is powered by a 3.6 V nominal lithium-ion rechargeable battery. It is capable of stimulating the spinal cord nerves through the electrodes of the leads connected to any combination of the output terminals, using one programmable current source.

Patient remote control: The patient remote control is a handheld battery operated unit that the participant can use to turn the stimulation on and off and to change the stimulation programs/settings.

Charger: This charger is used to transcutaneously charge the IPG battery. It is a portable device powered by a rechargeable battery and can be held in one hand.

Clinician programmer: The clinician programmer is an off-the-shelf laptop installed with proprietary software to allow the programming of the IPG and participant remote control.

Lead anchors: Lead anchors may be used to secure the leads to the fascia, possibly preventing lead migration and/or lead strain.

We will be using cascade programming in both groups; this involves four pairs of electrode groups and each pair is switched on for 5 s before the next pair is switched on (Fig. 2). Therefore, in 20 s, the whole lead has been activated and the cycle repeats. The rationale is that this avoids overstimulation, mitigates against small degrees of lead migration and removes any need for reprogramming. During the study, as both groups are programmed identically and reprogramming is not expected, the risk is reduced for unblinding and subsequent bias.

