### Device Implantation

Under standard operating theatre practice, all participants will be implanted with the following equipment: 10 kHz Senza IPG and two octopolar (8 contact) leads.

The first of the two leads will enter the epidural space through a lumbar or lower thoracic epidural puncture. The lead will be advanced cranially in the epidural space to reach a final position, where contacts 4 and 5 span the T9/10 disc space shown by Anterior-Posterior fluoroscopy in the anatomical midline as per our pilot experiment (Fig. 2). A lateral image will be obtained to ensure the lead is placed posteriorly in the epidural space.

Once satisfactory epidural lead placement is confirmed, the lead will be anchored to the deep fascia or supraspinous ligament and a strain relief loop will be established. The active epidural lead will be tunnelled to a subcutaneous pocket for the battery using an extension if necessary. This subcutaneous pocket is made in the gluteal region via a small skin incision and blunt subcutaneous dissection. This pocket should be large enough to accommodate the IPG, extensions and sham lead. This active lead (AL) will be used to provide therapy to the intervention group. The AL will be connected to the first or top port of the IPG in all participants, and a second sham lead (SL) will be inserted subcutaneously and attached to the second port of the IPG (Fig. 3). Impedances to check electrical integrity of the system will be performed at this time. Information will be given about wound care, and the device will remain ‘off’ until the participant’s next visit. Removal of sutures (if necessary) will be done at the implantation site.

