#### Blinding

Patients, investigators, outcome assessors and analysts will all be blinded. Only two study nurses at each site will be unblinded to the treatment received by the participants.

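### The activation-visit procedure gives allocation-dependent programming to blinded staff, which contradicts the limit of two unblinded nurses per site

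*Protocol article*

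**What the plan says.** Randomisation and Device Activation (Protocol article) sets out the visit as one list, introduced by "Firstly, the following will be performed by blinded study personnel". The list covers a check for adverse events, new X-rays, issue of the pain diary with instructions and, last, programming: the participant's "device and lead will be programmed according to their allocated group". The same item adds that "whereas the lead is different, the programming parameters used are identical". The text then moves straight to the follow-up phase. No step for unblinded staff is given.

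Device Implantation fixes how the leads are connected: "The AL will be connected to the first or top port of the IPG in all participants", with the sham lead on the second port. It also says "This active lead (AL) will be used to provide therapy to the intervention group".

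The Blinding section states "Patients, investigators, outcome assessors and analysts will all be blinded", and then "Only two study nurses at each site will be unblinded to the treatment received by the participants". The article gives these nurses no task.

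**The concern.** The arms differ only in which of two implanted leads is driven. Selecting that lead is therefore the act that puts the allocation into effect, and the visit procedure gives it to staff who are meant not to know the allocation.

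The Introduction says the trial was designed to separate the specific effect of stimulation from placebo response and from reporting bias in patients or assessors. The primary outcome is a self-reported pain diary, so staff who know the arm could influence it through cues. Adverse events are also recorded by staff. If a programmer labelled as blinded went on to do follow-up assessments, the safeguard on which the trial rests would be weakened.

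**Working it through.** No formula or figure is involved. The check compares four sections of the Protocol article.

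1. **When staff handling first differs by arm.** The Abstract places randomisation after the full implant, and every participant receives both leads. Neither the implantation nor an X-ray showing both leads reveals the arm. The first allocation-dependent act is programming at the activation visit.

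2. **Whether programming reveals the arm.** The programming item says the lead differs between groups while the parameters do not. Device Implantation fixes the mapping for everyone:
   - top port = epidural lead = intervention
   - second port = sham lead = control

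   Because the mapping never varies, choosing the port is the same as knowing the arm. The article describes no coded or masked programming that would break this link.

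3. **Whether identical programming removes the problem.** Under Identification and Description of the Investigational Device the article argues that "as both groups are programmed identically and reprogramming is not expected, the risk is reduced for unblinding and subsequent bias". This concerns the stimulation settings and the expected lack of later adjustments. It does not reach the choice of lead at activation, which is the one thing that separates the groups.

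4. **Who does it.**

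| Section | Who programs, or who may know the arm |
|---|---|
| Randomisation and Device Activation | Blinded study personnel carry out every listed task, including programming by allocation |
| Blinding | Only two nurses per site know the arm; no task is assigned to them |

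By steps 2 and 3 the programmer knows the arm. By the first row of the table the programmer is blinded. By the second row nobody except the two nurses may know. These statements cannot all hold.

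5. **How far it reaches.** Programming takes place once per participant at activation, so the contradiction touches every activation visit. This does not depend on the total sample size.

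**The case against.** The strongest reply is that this is a drafting slip. The list is announced as a first step and nothing follows it, while the Blinding section provides two unblinded nurses per site who have no stated task. Allocation-dependent programming is the obvious task for them. The likely intention is therefore a second, unblinded step that was run into the first list. This is plausible, and the point should be read as an inconsistency in the text and not as evidence that the sponsor chose to have blinded staff program devices. It does not remove the need for correction, because this list is the article's only description of who programs.

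A second reply is that a journal article condenses the full protocol. That would answer a complaint about missing detail. Here the article assigns the task expressly, and to the wrong role. The reply does have force against treating the absence of detailed delegation rules as a fault in itself, and no such fault is alleged.

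A third reply is that the route to bias is narrow, and much of this stands:
- Patients complete the diary themselves and are blinded.
- In the listed order, the adverse-event check and diary instruction precede programming, and the device stays off until this visit. Events recorded in that order predate any difference in stimulation.
- The Blinding section already requires outcome assessors and analysts to be blinded, which keeps staff known to be unblinded out of those roles. The gap is that the visit list labels the programmer as blinded, so that rule would not by itself exclude the programmer from follow-up assessment.

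**Conclusion.** The contradiction is real and must be reconciled. As written, the procedure would reveal the allocation at each activation visit to a staff member designated blind, contrary to the limit of two unblinded nurses per site. This rests on the fixed port mapping, on the absence of any masked programming method in the article, and on no break separating the programming item from the rest of the list; the text shows none.

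The consequences for bias are conditional. Three stronger readings may be inferred, and the documents do not support them:
- **That the staff concerned know the allocation throughout follow-up.** The article does not say that one person does every listed task, or that the programmer is also a follow-up assessor. The harm depends on that overlap, which is neither stated nor ruled out.
- **That the allocation-guess check is defeated by design.** This too needs the overlap. Assessors guess after each follow-up assessment and at the end of the study, and an excess of correct guesses could itself expose unblinding.
- **That unblinding has occurred in every participant.** The article shows what its text would lead to if followed. It does not show which section sites have followed.

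**What to change.** Take programming out of the list for blinded personnel and make it a separate step for the unblinded nurses described in the Blinding section. Give the same nurses any later device interrogation or reprogramming. Add one sentence saying that they take no part in follow-up assessment of outcomes or adverse events.

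The cost is a rewording of the visit procedure and an entry in the delegation log; the nurses are already in the plan at each site. Trial Status reports recruitment under way, so existing delegation logs could also be checked to confirm who has been programming.

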### After 6-month Follow-up

After the 6-month visit all patients will be managed in the standard pain management service, outside the trial.

### Medication Usage

All medications prescribed for the treatment of pain will be recorded during the screening visit. Only participants who are on a stable dose of all prescribed pain medications for at least 4 weeks prior to screening and willing to maintain or decrease the dose of all prescribed pain medications are eligible for participation in this study. Any changes to an enrolled participant’s pain medications during the study will be recorded.

The addition of pain medications for the relief of surgical discomfort after implant procedures is allowed. Pain medications prescribed for short-term post-operative pain management are not considered an increase in pain medications if the medication is ceased and the medication end date is prior to the date of randomisation.

All medications used to treat adverse events (regardless of the reason prescribed) will be documented as interventions on the Event CRF.

### Sample Size

For our primary outcome of pain severity VAS (0-100 mm), the Initiative on Methods, Measurement and Pain Assessment in Clinical Trials (IMMPACT) proposes a minimally important clinical difference (MICD) of 20 mm [27]. To detect this MICD and based on a back/leg pain VAS standard deviation of 25 mm, as seen in previous conventional and 10Khz-SCS RCTs set at 90% power and 5% alpha, and a worst case attrition rate of 30% at 6-months follow up, we will need to recruit 96 participants (48 per centre) per group.

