**Methods:**

This is a multicentre, double-blind, randomised, sham-controlled trial with a parallel economic evaluation. A total of 96 patients with CNLBP who have not had spinal surgery will be implanted with an epidural lead and a sham lead outside the epidural space without a screening trial. Patients will be randomised 1:1 to 10 kHz SCS plus usual care (intervention group) or to sham 10 kHz SCS plus usual care (control group) after receiving the full implant. The SCS devices will be programmed identically using a cathodal cascade. Participants will use their handheld programmer to alter the intensity of the stimulation as per routine practice. The primary outcome will be a 7-day daily pain diary. Secondary outcomes include the Oswestry Disability Index, complications, EQ-5D-5 L, and health and social care costs. Outcomes will be assessed at baseline (pre-randomisation) and at 1 month, 3 months and 6 months after device activation. The primary analyses will compare primary and secondary outcomes between groups at 6 months, while adjusting for baseline outcome scores. Incremental cost per quality-adjusted life year (QALY) will be calculated at 6 months and over the lifetime of the patient.

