### Study Setting

Participants will be recruited from two neuromodulation centres: Guy’s & St. Thomas NHS Foundation Trust, London, UK, and South Tees Hospitals NHS Foundation Trust, Middlesbrough, UK.

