#### Allocation Concealment

Patients will be allocated 1:1 to intervention or control and were stratified by centre using a web-based computer-generated random-allocation sequence to ensure concealment. This website will be password protected and managed by Exeter CTU.

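### The Sample Size section sets 96 participants per group (192 in all), but its own inputs and the abstract give 96 in total

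*Protocol article*

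**What the plan says.** The Sample Size section of the protocol article gives a complete set of inputs for the primary outcome, back pain on a 0-100 mm VAS:

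- a "minimally important clinical difference (MICD) of 20 mm";
- a "back/leg pain VAS standard deviation of 25 mm";
- the calculation "set at 90% power and 5% alpha";
- "a worst case attrition rate of 30% at 6-months follow up".

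It then concludes: "we will need to recruit 96 participants (48 per centre) per group".

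The Methods paragraph of the abstract gives a different size: "A total of 96 patients with CNLBP who have not had spinal surgery will be implanted", followed by 1:1 randomisation. Two other sections fix how these numbers divide. Allocation Concealment says "Patients will be allocated 1:1 to intervention or control", and Study Setting says "Participants will be recruited from two neuromodulation centres".

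**The concern.** The two statements cannot both hold. The Sample Size sentence attaches the 96 to each group, so the trial would recruit 2 × 96 = 192. The abstract's 96 is the whole trial, which is 48 per group.

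The wording in Sample Size is also coherent on its face, because two centres at 48 each do make 96 in each group. Nothing inside the sentence warns the reader. The error shows only when the calculation is repeated or the abstract is compared.

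According to Device Implantation, every participant, sham arm included, receives a pulse generator and two leads, one of them epidural. Taken literally, the Sample Size section asks for 96 more surgical implants than its stated power needs. If recruitment instead stops at 96, anyone checking enrolment against that section will conclude that the trial reached half its target. Trial Status describes recruitment as under way, so the target was still in force at publication.

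**Working it through.** **Inputs.** From Sample Size: difference δ = 20 mm, SD σ = 25 mm, power 90%, alpha 5%, attrition 30%. From Allocation Concealment: ratio 1:1. Sidedness is not stated; two-sided is assumed first and one-sided is tried afterwards.

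**Step 1. Evaluable number per group, normal approximation.**

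n = 2 (z₀.₉₇₅ + z₀.₉₀)² (σ/δ)² = 2 × (1.960 + 1.2816)² × (25/20)² = 32.8, so 33 per group.

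**Step 2. Allow for 30% attrition.**

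33 / (1 − 0.30) = 47.1, so 48 per group and 2 × 48 = **96 in total**. This reproduces the abstract's figure exactly.

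**Step 3. Same calculation with the t distribution.**

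33 per group gives 89.3% power and 34 per group gives 90.2%, so 34 are needed. 34 / 0.70 = 48.6, so 49 per group and 98 in total, within 2 of the abstract's figure.

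**Step 4. Can any variant give 96 per group?**

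| Variant | Evaluable per group | Recruited per group | Total |
|---|---|---|---|
| Two-sided, normal, n/(1 − 0.30) | 33 | 48 | 96 |
| Two-sided, t, n/(1 − 0.30) | 34 | 49 | 98 |
| One-sided, normal or t, n/(1 − 0.30) | 27 to 28 | 39 to 40 | 78 to 80 |
| Two-sided, inflated as n × 1.30 | 33 to 34 | 43 to 45 | 86 to 90 |

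None does. The alternatives to the first two rows all give fewer than 48 per group.

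**Step 5. What each reading would deliver (two-sided).**

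- *96 in total:* 48 × 0.70 = 33.6 evaluable per group, and power for 20 mm is about 89.8%. This agrees with the stated 90%.
- *96 per group:* 96 × 0.70 = 67.2, about 67 evaluable per group, and power for 20 mm is about 99.6%. The difference detectable with 90% power would be (1.960 + 1.2816) × 25 × √(2/67) = 14.0 mm, not 20 mm. Put the other way, 90% power for 20 mm would correspond to an SD of about 35.7 mm, not 25 mm.

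**Step 6. Source of the mismatch.** With two groups and two centres, 96 in total is 96/2 = 48 per group and, if the centres recruit equally, 96/2 = 48 per centre. The sentence's 96 and 48 are both right for the trial as a whole. Only the closing words that assign the 96 to each group do not fit.

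**The case against.** The strongest reply is that this is a slip of wording and not a fault in the calculation. The inputs are sound, the correct total stands in the abstract, and a reader who repeats the calculation will recover it. Nothing in the article shows 192 being used in practice, and the abstract says outright how many people are to be implanted. On that view the 96 extra implants are hypothetical, and the real risk is a misreading of the final enrolment.

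Most of this stands. The misplaced phrase is the likeliest explanation, the trial is not shown to be underpowered, and there is no evidence that anyone is recruiting to 192.

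It does not remove the point. Sample Size is the section that defines the target, and as worded it gives a definite number that its inputs do not support. That the article condenses a longer protocol may explain omitted detail, but not a wrong result stated next to all of its inputs.

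Two smaller reservations are fair. Sidedness is an assumption here, and the exact match to 96 depends on the normal approximation, since the t-based total is 98. Neither brings 96 per group within reach.

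**Conclusion.** The concern holds. The Sample Size section is wrong as written and contradicts the abstract. Its inputs support 33 to 34 evaluable and 47 to 49 recruited per group, about 96 in total. The stated target of 96 per group is twice that, a difference of 96 implanted participants. The conclusion assumes an unadjusted comparison of two means with the stated SD. It does not depend on whether alpha is one-sided or two-sided, on the normal or t calculation, or on how attrition is applied. It is an error in the stated target, most likely of wording, and no criticism of the trial's power: at 96 in total, power is about 89.8% against the stated 90%. It should be corrected because the target size is a figure on which the trial and its later report rely.

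**What to change.** Reword the conclusion of Sample Size to give 96 participants in total (48 per group; 48 per centre). Add the evaluable number behind it, about 33 to 34 per group after 30% attrition, and say that alpha is two-sided if that is the case. Then check that the full protocol, the SAP and the registry entry carry the same total; they were not available here, so whether they repeat the error is unknown.

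The cost is one sentence. Recruitment does not change if 96 in total is already the working target. If 192 was in fact intended, the inputs would have to be restated, because those given do not lead to it.

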### Recruitment

Recruitment will be from outpatients of the two centres. The study will be presented in national and international meetings to a target audience of pain physicians, spinal surgeons, neurosurgeons and physiotherapists. Advertising will be conducted through newspapers and magazines to enhance recruitment. Road shows were organised to target spine surgeons, neurosurgeons and pain physicians.

